### Statistical analyses

Receiver Operating Characteristic (ROC) curves have been used in an earlier stage to find the optimal cut-off point of the venous H-FABP-test [8]. Using 2 × 2 tables and multivariate analyses, including CART analysis, multiple logistic regression, or both, the diagnostic value of the H-FABP-test in combination with clinical findings for ACS and AMI will be assessed [49,50]. Our analysis will result in PPVs and NPVs, sensitivity and specificity and their 95% confidence intervals. Additionally, C-statistics will be presented to quantify overall prediction quality of the models.

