## Background

### Daily practice

Patients presenting with chest complaints caused by acute coronary syndrome (ACS) need urgent transport to a specialist setting [1,2]. In these situations, favourable outcome is inversely related to the time interval between onset of complaints and vascular rescue treatment. However, in daily practice, most patients experiencing chest complaints primarily apply to a general practitioner (GP). Within this population, benign conditions such as thoracic wall complaints, gastric disease or psychiatric and somatoform disease, largely outnumber cases of ACS [3-5]. In specialised care facilities such as coronary care units, 50% of patients presenting with chest pain are diagnosed with ACS, whereas in primary care, ACS is diagnosed in no more than 1.5-22% of cases [6-8]. Referring every patient with chest complaints would overwhelm secondary care facilities, however the GP is faced with serious diagnostic dilemmas since milder diseases with beneficial outcome can mimic ACS and vice versa [9]. Safe exclusion, rather than inclusion, is the main task of a GP in assessing chest complaints.

In primary care, where clearly circumscribed diseases with specific symptoms are embedded in a broad scope of illness and mild disease with less typical appearance, discriminative signs are usually scarce. This applies in particular to ACS, where history, physical examination and electrocardiography notoriously lack sensitivity and specificity as has been extensively surveyed [10-12]. With regard to chest pain, only few signs and symptoms, for example, the absence of pain on chest palpation or presence of pain on exertion, generate discriminative strength in diagnostic studies, although to a limited extent [9,13,14]. Altogether, clinical signs and symptoms are inappropriate for ruling out ACS or lack additive value above the clinical judgment by the GP, which on itself is correct in a majority of cases [6]. Weighing more abstract factors (e.g. contextual patient factors and altered presentation in time) probably leads to this fairly adequate clinical judgment of GPs [15-17].

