### Study design and objectives

This current study is a derivation study to identify signs and symptoms that, combined with point of care heart-type fatty acid-binding protein (PoC H-FABP) testing, can be part of an algorithm to confirm or rule out ACS (meaning AMI and unstable angina (UA)) and AMI alone in a population of patients with complaints possibly due to myocardial ischaemia in general practice. Thus, stage 2 of the 6 major stages in the development and testing of a clinical decision rule as defined by Stiell and Wells will be studied [42]. The diagnostic value of the algorithm will be studied and compared to regular assessment by a GP without PoC H-FABP testing using a delayed type cross-sectional diagnostic model. Both ACS and AMI as a subgroup of ACS will be analysed as final diagnosis. The cost-effectiveness of the test will also be evaluated. The study commenced in November 2013 and will run for two years. External validation of the algorithm derived from this study needs to be performed in future studies.

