## Methods

### Recruitment

Two hundred and ten GPs in four regions in the South and Southeast of the Netherlands and the Northeast of Belgium, including both urban and rural areas, will be informed by e-mail of our study and given the opportunity to respond. The first 60 GPs that decide to participate will receive a detailed training in using the test and performing all relevant research activities in order to include ten successive eligible patients, making a total of 600 patients. Inclusion will take place at any time during the day and night, including either during consultation in a primary care facility or during home visits by participating GPs. During evaluations in the study period with participating GP’s, adherence to the protocol and actual recruitment of consecutive cases will be checked and reported.

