### Primary and secondary outcome

The most important feature of the algorithm of signs and symptoms combined with PoC H-FABP testing will be to adequately categorise all patients as either positive or negative for ACS. The ability of the algorithm to rule in UA in the ACS group is important, since UA is a condition that does not give a rise in biomarkers and diagnosis depends exclusively on signs and symptoms.

Primary outcome: using multivariate analysis of our data, signs and symptoms that have diagnostic value in an algorithm to predict or exclude ACS and AMI will be identified. The primary outcome measures of the study will be *s*ensitivity, specificity, positive and negative predictive value of an algorithm of those relevant signs and symptoms combined with PoC H-FABP testing for ACS and AMI, in patients with thoracic complaints of new onset in general practice. To determine influence of sex, age, duration of the complaints, and kidney function on clinical performance of H-FABP-testing, subgroup analyses within our study population will be performed [47,48].

Secondary outcome: an economic evaluation by means of an incremental cost-effectiveness ratio (ICER) will be performed. This evaluation will be performed by determination of the ratio between the difference in medical costs and the difference in benefits between the two strategies that are observed in this study, being the usual reference policy of the GP and the reference policy that could be created using a determined algorithm consisting of a clinical score and PoC H-FABP-testing. The benefits will be described as reduction in number of referred patients versus missed diagnoses if the algorithm is used.

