### Sample size and power calculation

An incidence of ACS of 22% would generate 132 patients with ACS and 468 patients without ACS in a study population of 600 patients. To create a usable algorithm consisting of signs, symptoms and H-FABP, the sensitivity of this algorithm should reach 85-90% and specificity should reach 80-85%. In a worst case scenario, where sensitivity would be 85% and specificity would be 80%, combined with the incidence of ACS of 22%, PPV of the algorithm of signs, symptoms and H-FABP for ACS would be 54% (95% C.I. 47-61%) and the NPV 95% (95% C.I. 93-97%). These diagnostic values with their 95% C.I. would be of significant interest, since PPV based on clinical judgment only is 22% and NPV is 95%. Therefore, a sample size of 600 generates adequate precision to find clinically relevant improvement of PPV, as compared to the current situation, and NPV that is at least not diminishing.

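### The algorithm is derived and its primary accuracy reported in the same 600 patients with no stated optimism correction, and the rule-out (NPV) claim has no margin to absorb the expected bias

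*Protocol article*

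**What the plan says.** Under Primary and secondary outcome, the predictors come out of the study's own data: "signs and symptoms that have diagnostic value in an algorithm to predict or exclude ACS and AMI will be identified". The sensitivity, specificity, PPV and NPV of the algorithm built from them, together with H-FABP, are the primary outcome measures, for both ACS and AMI.

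Statistical analyses names the technique as "multivariate analyses, including CART analysis, multiple logistic regression, or both" and continues: "Our analysis will result in PPVs and NPVs, sensitivity and specificity and their 95% confidence intervals". C-statistics are added. The section mentions no split sample, cross-validation, bootstrap or shrinkage, and does not say how the intervals will be calculated.

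Validation appears only as later work. Study design and objectives says "External validation of the algorithm derived from this study needs to be performed in future studies", and the Discussion likewise assigns validation to the stages after this one.

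The study size is set under Recruitment ("in order to include ten successive eligible patients, making a total of 600 patients"). The section Sample size and power calculation justifies it from these expected counts: "An incidence of ACS of 22% would generate 132 patients with ACS and 468 patients without ACS in a study population of 600 patients".

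**The concern.** A rule chosen because it fits 600 patients looks better in those patients than in new ones. Selecting predictors, choosing between a tree and a regression, and placing a cut-off on the final score all use the outcome data, so accuracy computed in the same patients is apparent accuracy.

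Three features of the plan make this more than a technicality:

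- The comparator is not fitted. Under Data collection, the GP's referral decision is recorded before the test result is read. Only the algorithm gains from fitting, so the comparison leans its way.
- The safety quantity is missed ACS, which is where NPV and sensitivity enter.
- The ICER sets referrals avoided against missed diagnoses, so it inherits any understatement of misses.

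**Working it through.** **Step 1: the plan's own figures.** Inputs from Sample size and power calculation: N = 600, incidence 22%, sensitivity 85%, specificity 80%.

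- ACS cases: 600 × 0.22 = 132; non-cases: 468
- True positives: 132 × 0.85 = 112.2; false negatives: 19.8
- True negatives: 468 × 0.80 = 374.4; false positives: 93.6
- PPV = 112.2 / 205.8 = 54.5%; Wald 95% CI ± 1.96 × √(0.545 × 0.455 / 205.8) = ± 6.8 points, so 47.7 to 61.3%
- NPV = 374.4 / 394.2 = 95.0%; Wald 95% CI ± 1.96 × √(0.950 × 0.050 / 394.2) = ± 2.2 points, so 92.8 to 97.1%

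The plan states 54% (47 to 61%) and 95% (93 to 97%). These agree to within a point of rounding. The formulas treat the algorithm as fixed in advance, which it is not. Even on that footing, the NPV interval reaches below the GP's 95%.

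**Step 2: illustrative size of the optimism.** The article does not give the number of candidate predictors, their effects, the selection rule or the cut-off rule, so these are assumptions: 8, 20 or 30 candidates, of which eight truly predict; effects tuned to roughly 85% sensitivity and 80% specificity; backward elimination at p < 0.10; score cut-off set at an apparent sensitivity of at least 85%. There were 300 data sets of 600 patients per setting. True performance was taken from 50,000 independent patients. Coverage is that of ordinary Wald 95% intervals for the true value.

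Each pair is apparent → true:

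| Setting | Sensitivity % | NPV % | C | Coverage, sensitivity / NPV |
|---|---|---|---|---|
| Logistic, 8 candidates, 22% ACS | 85.3 → 82.9 | 95.0 → 94.2 | 0.899 → 0.889 | 87% / 87% |
| Logistic, 20 candidates, 22% | 85.4 → 82.2 | 95.0 → 94.1 | 0.904 → 0.888 | 79% / 84% |
| Logistic, 30 candidates, 22% | 85.4 → 80.9 | 95.1 → 93.6 | 0.907 → 0.882 | 67% / 71% |
| Unpruned CART (minimum leaf 20), 20 candidates, 22% | 87.3 → 76.8 | 95.3 → 91.4 | 0.891 → 0.806 | 7% / 9% |
| Logistic, 20 candidates, 5% ACS (30 cases) | 86.7 → 72.8 | 99.2 → 98.4 | 0.941 → 0.899 | 50% / 54% |

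For logistic regression at 22%, the differences are 2.4 to 4.5 points in sensitivity, 0.8 to 1.5 points in NPV and 0.010 to 0.025 in C.

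**Step 3: what that means for missed cases.** Per 132 ACS cases:

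- 8 candidates: reported misses 132 × 0.147 = 19.4; true misses 132 × 0.171 = 22.6
- 30 candidates: reported misses 132 × 0.146 = 19.3; true misses 132 × 0.191 = 25.2

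That is about 3 to 6 misses not shown.

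**Step 4: PPV.** In the same logistic runs, PPV falls from 52.6 to 51.5% (8 candidates) and from 54.5 to 51.9% (30 candidates). In the most overfitted tree tried (minimum leaf 10), it falls from 57.7 to 46.0%. All remain at least twice the GP's 22%.

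**Step 5: number of cases.** The 132 is at the upper end of the article's own range: under Daily practice, "in primary care, ACS is diagnosed in no more than 1.5-22% of cases". AMI, analysed as a subgroup of ACS, must have fewer cases than ACS. Fewer cases mean more optimism, as the 5% row shows.

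**The case against.** The strongest reply is that this is a condensed article. Resampling, the candidate list and the interval method are usual contents of a full protocol or analysis plan, which may exist. That stands to this extent: a reader might infer that no internal validation will be done, but the article only fails to state one and nowhere rules it out. What remains is what the article does fix: data-driven selection, an open choice of technique, accuracy in the same patients as the primary outcome, and validation mentioned only for later studies.

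Second, the study is labelled a derivation study, external validation is called for, and there is no non-inferiority test or adoption rule. This limits the harm, and no clinical rule follows directly from these estimates. It does not correct the figures that the study will publish, compare with the GP and enter in the ICER.

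Third, the H-FABP threshold of 4 ng/ml is set beforehand. That removes one usual source of optimism. It leaves predictor selection, technique and the cut-off on the combined score.

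Fourth, the bias is modest beside sampling error: for 85% of 132 cases the 95% half-width is 1.96 × √(0.85 × 0.15 / 132) = 6.1 points. That is correct, but sampling error is displayed by an interval and has no direction. Optimism is not displayed and always flatters the algorithm.

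Fifth, the text does not say that the technique will be picked on its results. That is correct too; the point is only that nothing prevents it.

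**Conclusion.** The point holds, as should-fix. Followed as written, the analysis yields apparent accuracy. Its sensitivity, NPV and C-statistic are expected to be optimistic, and specificity and PPV too, though less so when the cut-off is set on sensitivity. With 132 cases, logistic regression and 8 to 30 candidates, expect about 2 to 4.5 points in sensitivity, 1 to 1.5 in NPV and 0.01 to 0.025 in C, with coverage of about 67 to 87%. Unpruned trees or fewer cases would be worse. All of these sizes rest on the assumptions in the working; only the direction is general.

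The consequence lies in rule-out. The sample size argument needs an NPV no lower than the GP's, and both are 95%, so a bias of about one point is enough to hide a shortfall.

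Three stronger readings are not supported:

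- That the intervals are invalid: no interval method is named, and in the mildest setting coverage is 87%, which is under-coverage.
- That the expected PPV gain (54% against 22%) is an artefact: optimism of this size does not threaten it.
- That the larger bias seen with a lower incidence or a cut-off at 90% sensitivity is the expected one: the sample size section plans on 22%, and the article fixes no cut-off rule.

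**What to change.** In Statistical analyses, before data lock:

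1. State which modelling route gives the primary algorithm, and the rule for placing the cut-off on its final score. Either technique will do, provided it is named.
2. Repeat the entire derivation (predictor selection, any choice between techniques, cut-off) in bootstrap resamples or by cross-validation, separately for ACS and AMI.
3. Report optimism-corrected sensitivity, specificity, PPV, NPV and C-statistic as the primary figures, with intervals from the same resampling and the apparent values beside them.
4. Use the corrected values in the comparison with the GP's decision and in the ICER.

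If an unpublished protocol or analysis plan already provides this, a sentence pointing to it is enough.

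The cost is some programming and slightly less favourable reported accuracy. No extra patients or data are needed.

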### Ethical considerations

The outcome of the test will be subject to this diagnostic study and can therefore have no clinical consequence on the GP’s decision. Patients willing to take part in this study will mainly be treated as usual. Only a finger prick blood analysis for H-FABP will be added to the normal procedure and venous blood sampling will be added in patients that are not referred to secondary care facilities. This study will be in agreement with the current version of the WMA Declaration of Helsinki and will be in accordance with the Dutch Medical Research Involving Human Subjects Act (WMO, http://wetten.overheid.nl/BWBR0009408/geldigheidsdatum_29-10-2013) [51]*.* An independent expert will be available in both countries throughout the study and contact data of this expert will be given to all participating patients. This study protocol has been approved by the ethical review board of Maastricht University for the Netherlands and by the ethical review board of KU Leuven for Belgium. Full research procedures are registered on www.clinicaltrials.gov, NCT01826994.

All GPs including patients for our study will have a liability insurance themselves or via the centre they work for. Maastricht University and KU Leuven have an insurance covering damage to research subjects through injury or death caused by the study, that becomes apparent within 4 years after the end of the study.

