GPs will be instructed to base their referral decisions on the current guidelines on ACS, as is common in the Netherlands and Belgium [43]. Participating GPs will be informed that the PoC H-FABP test is currently under study and that the test results should not influence their decision to refer. Only in the few cases that a PoC H-FABP test is positive after an initial decision not to refer, referral policy will be different from usual care since in that rare occasion, the GP is advised to refer. By following the registration work up as mentioned above, we can still conclude that principally, a referral wouldn’t have been made.

Patients that are not referred to secondary care will be instructed and facilitated to have a venous blood sample drawn within the interval between three hours to three days after onset of complaints. Test results will be primarily used to exclude AMI in non-referred patients based on hsTn analysis. However, the GP is instructed to take notice of the result. If the troponin value is elevated, referral to a cardiologist must take place. Furthermore, renal function, based on creatinine and glomerular filtration rate using MDRD-formulas, will be determined. Collected samples will be preserved for a maximum of 15 years for possible future analysis when relevant.

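### The ethics text says the H-FABP result has no clinical consequence, yet the data-collection text advises referral after some positive results, so verification partly depends on the index test

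*Protocol article*

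**What the plan says.** All references are to the protocol article.

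- **Ethical considerations:** "The outcome of the test will be subject to this diagnostic study and can therefore have no clinical consequence". The sentence refers to what the GP decides. The section adds that patients are mainly treated as usual. It lists two additions only: the finger prick, and venous sampling in patients who are not referred. Referral prompted by the test is not mentioned.
- **Data collection, general rule:** GPs are told that "the test results should not influence their decision to refer".
- **Data collection, exception:** where a positive result follows a recorded choice against referral, cases which the plan describes as few, "referral policy will be different from usual care since in that rare occasion, the GP is advised to refer". The section argues that the usual decision remains known, because the GP records it before the test.
- **Data collection, non-referred patients:** one venous sample is taken between three hours and three days after onset. It serves mainly to exclude AMI by high-sensitivity troponin (hsTn). An elevated value also leads to referral.
- **Final diagnosis:** the team collects data from the GP at 30 days and, for referred patients, from the hospital where necessary. The expert panel is blinded to the point-of-care result and sees all other data.
- **Primary and secondary outcome:** ACS includes unstable angina (UA), which the plan says gives no biomarker rise. The ICER uses differences in costs and benefits "between the two strategies that are observed in this study".

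**The concern.** The first problem is textual. The ethics section describes a study in which the result changes nothing for the patient; the data-collection section describes one in which it can lead to referral. The Informed consent section supports its shortened consent procedure by saying that most of what is done is regular care, so the account of what the test can trigger should be accurate.

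The second problem follows if the exception stands. Among patients the GP would not refer, the index result then helps decide how the diagnosis is verified. A positive result can bring a hospital work-up. A negative result brings the lighter route, whose blood test cannot show UA. ACS missed in test-negatives is counted as a true negative, which flatters sensitivity and NPV. NPV matters most here, because the stated purpose is safe exclusion and the Sample size section requires that NPV at least not diminish from 95%.

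**Working it through.** The contradiction needs no arithmetic: one section denies any consequence for the GP's decision, and the other advises a change of decision after a positive result. The plan gives no figure for how often this occurs, so the size below is built from its other figures and from stated assumptions.

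**Inputs from the document.** N = 600 and ACS incidence 22% (Sample size and power calculation). GP sensitivity 81% and specificity 55%, with PPV 22% and NPV 95% (Background, Daily practice).

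**Inputs assumed.** H-FABP sensitivity 50-85% and specificity 80-95% in this population; the document gives neither. H-FABP is taken as independent of the GP's decision, given disease status.

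**Step 1: prevalence.** 600 × 0.22 = 132 with ACS and 468 without, as the plan states. At 22%, however, the GP figures give PPV (0.81 × 132)/(0.81 × 132 + 0.45 × 468) = 33.7%, not 22%. At 13.5% (81 and 519 patients) they give PPV 65.6/(65.6 + 233.6) = 21.9% and NPV 285.5/300.8 = 94.9%, matching the quoted values. Both prevalences are carried forward.

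**Step 2: initially not referred** = 0.19 × ACS + 0.55 × non-ACS.
- At 22%: 25.1 + 257.4 = 282.5.
- At 13.5%: 15.4 + 285.5 = 300.8.

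**Step 3: of these, H-FABP positive** = sensitivity × ACS part + (1 − specificity) × non-ACS part.
- 22%, low end (50%, 95%): 12.5 + 12.9 = 25.4, or 4.2% of 600.
- 22%, high end (85%, 80%): 21.3 + 51.5 = 72.8, or 12.1%.
- 13.5%, low end: 7.7 + 14.3 = 22.0, or 3.7%.
- 13.5%, high end: 13.1 + 57.1 = 70.2, or 11.7%.

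The span is about 22 to 73 patients, or 4-12% of the sample.

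**Step 4: effect on apparent H-FABP sensitivity.** Suppose the lighter route misses a fraction m of ACS in non-referred test-negatives (assumed 25-75%), and every other patient is classified correctly. Prevalence cancels:

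apparent sensitivity = Se / [Se + (1 − Se)(1 − 0.19m)]

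- Se 50%: 0.5/0.97625 = 51.2% to 0.5/0.92875 = 53.8%.
- Se 70%: 0.7/0.98575 = 71.0% to 0.7/0.95725 = 73.1%.
- Se 85%: 0.85/0.99288 = 85.6% to 0.85/0.97863 = 86.9%.

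The rise is about 1 to 4 points.

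**Step 5: effect on apparent H-FABP NPV at 22%.** The missed cases move from false to true negatives.
- Largest (Se 50%, Sp 80%, m = 0.75): 66 false and 374.4 true negatives; missed 0.75 × 0.19 × 66 = 9.4. NPV goes from 374.4/440.4 = 85.0% to 383.8/440.4 = 87.1%.
- Smallest (Se 85%, Sp 95%, m = 0.25): 19.8 false and 444.6 true negatives; missed 0.25 × 0.19 × 19.8 = 0.9. NPV goes from 444.6/464.4 = 95.7% to 445.5/464.4 = 95.9%.

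The rise is about 0.2 to 2.1 points.

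**The case against.** Most of the other side's case has force and limits the point.

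- **A rule with an exception.** A reader might infer that GPs hold two opposite instructions. Data collection read alone does not support that: it states a rule, marks an exception and admits the departure from usual care. Nothing shows that GPs receive the ethics text as an instruction. The conflict is between the two sections.
- **The recorded decision is protected.** It is filled out before the test, so the usual-care referral comparator is sound. This stands, but it does not make verification independent of the test.
- **The lighter route is more than one blood sample.** Non-referred patients also have 30-day data from the GP and panel adjudication. The panel has the recorded signs and symptoms, on which the plan says UA diagnosis depends. AMI is covered by hsTn in all of them. This keeps the bias modest and confines it mainly to UA. Blinding governs how the panel reads the data, though, not which data exist.
- **Patients already referred are unaffected.** They go to hospital whatever the result.
- **PPV.** A reader might infer that PPV is inflated too. It is computed among test-positives only, and fuller work-up there can rule ACS out as well as in; it does not push PPV above its true value.
- **Costs.** A reader might infer that usual-care cost is overstated in the ICER. That holds only if observed costs are used without reassigning test-driven referrals. The plan names the GP's usual policy as the comparator and nowhere charges such referrals to it.

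**Conclusion.** The contradiction is explicit, and the ethics statement is wrong as written if the referral advice stands. In that case the index result sets the verification route, but only among patients initially not referred. The likely bias is in sensitivity and NPV for ACS, through missed UA in test-negatives.

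The size is modest: about 22 to 73 affected patients (4-12%), a rise of about 1 to 4 points in H-FABP sensitivity, and 0.2 to 2.1 points in NPV at 22% ACS. These rest on assumed H-FABP accuracy, an assumed miss rate of 25-75%, and independence of test and GP decision. They concern H-FABP alone; the effect on the final algorithm would depend on how it uses the test.

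It is tempting to conclude that the plan is mistaken in calling these cases few and rare. The document does not support going that far: it gives no figure either way, and about 4% could fairly be called few while 12% could not.

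**What to change.** 1. Reconcile Ethical considerations with Data collection, and any patient information that repeats either. Which rule stands is for the clinical team and ethics boards.
2. Identify patients with a decision not to refer before the test who were referred after a positive result. The pre-test decision, test result and 30-day referral data largely allow this. Also record the reason for the changed decision, since elevated troponin leads to referral too.
3. Keep these patients as not referred in the GP comparator, and state that their test-driven referral costs are not charged to usual care in the ICER.
4. Report ACS accuracy with a sensitivity analysis for missed UA in non-referred H-FABP-negatives, alongside the AMI result based on hsTn.
5. State the differential verification as a limitation.

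The cost is a wording amendment, one recorded reason and one extra sensitivity analysis. Sample size and recruitment are unchanged.
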